#### Secondary Objectives

We expect frequency of depression and anxiety in minor stroke population to be as high as frequency in general stroke. Indeed, even if the motor and cognitive impairments after a more severe stroke could lead to more severe anxiety and depression, previous study about prevalence of depression after minor stroke is in the range of prevalence found in general stroke population (Shi et al., 2015).

In line with previous results about PSD (Carota et al., 2005; Sibon et al., 2012; Lerdal and Gay, 2013), the results about the ecological characteristics of depression and anxiety after minor stroke could reveal different symptoms’ profiles as a function of time. Depression and anxiety at phase 1 would be characterized more by physical and non-specific symptoms such as fatigue, physical tension, attention difficulty whereas phase 2 and 3 profiles would have different profiles characterized by more specific symptoms.

Even if the investigation of time dynamics between depression and anxiety symptoms is greatly exploratory, we have similar expectations regarding the evolution of the importance and centrality of physical symptoms as function of time. Indeed, physical and non-specific would lead to more specific symptoms at phase 1 than at phase 2 and 3.

Results about coping strategies could follow the same pattern, with different adaptive and maladaptive coping at phase 1, 2, and 3. In regard of previous research (Darlington et al., 2007; Rochette et al., 2007), active coping would lead to less anxiety and depression at phase 1 than later.

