#### Sample Size

Forty participants will be included in the study. According to previous research using EMA for psychological assessment, an acceptance rate between 75 and 90% is expected (Johnson et al., 2009a,b). Thus, we expect data from 30 to 36 participants to perform analysis.

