##### Outcomes and statistical methods for secondary objectives

(1) Frequency will be estimated as the ratio of depressed and anxious participants to the total number of participants. Presence of depression and anxiety will be determined in two different ways: according to the examination of psychiatric disorders during the semi-structured interview; and as a function of the cut-off scores of self-reported questionnaires and clinicians’ ratings scale previously reported in the instruments section.

(2) Univariate logistic regression analysis will be performed to study if the clinical variables (subtypes of anxiety and depression symptoms, coping strategies) predict depression and anxiety within each time and between times of the study.

(3) Descriptive analysis will be performed on clinical, sociodemographic and medical measures to describe depressed and anxious participants. Their results will be compared to healthy participants (presenting no significant depression and anxiety) with Chi-square and Student’s *t*-test.

(4) We will examine whether EMA of the different symptoms of depression and anxiety are associated with self-report and clinician-rated depression and anxiety to describe characteristics of PSD and PSA. Means-as-outcomes modeling will be used to describe those associations.

(5) In order to describe the time dynamics between anxiety and depression symptoms, coping strategies and contextual settings assessed with EMA, we will use a Multilevel Vector Autoregressive method (Bringmann et al., 2013). With the Vector Autoregressive (VAR) model, each variable at time point *t* is regressed to the time point *t* – 1 of every other variable. For example, sadness at 1 pm is regressed with all other depression and anxiety symptoms (including sadness) at 10 am. The multilevel-VAR model is suited to the hierarchical structure of EMA data and it enables to describe population dynamics as a function of within-person variability.

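### The article expects the effect of active coping to change across phases, but the model named for coping gives no estimate or interval for that change

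*Protocol article*

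**What the plan says.** The Discussion of the protocol article (Anticipated Results, Secondary Objectives) expects that "active coping would lead to less anxiety and depression at phase 1 than later". Just before this, on symptom dynamics, it expects that "physical and non-specific would lead to more specific symptoms at phase 1 than at phase 2 and 3", after noting that the "investigation of time dynamics between depression and anxiety symptoms is greatly exploratory".

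The methods are under Outcomes and statistical methods for secondary objectives:

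- Item (2), predictors including coping: "Univariate logistic regression analysis will be performed to study if the clinical variables" (symptom subtypes and coping strategies) "predict depression and anxiety within each time and between times of the study".
- Item (4), symptom associations: "Means-as-outcomes modeling will be used to describe those associations". Phase is not mentioned.
- Item (5), dynamics between symptoms, coping and context: "we will use a Multilevel Vector Autoregressive method". Whether phases are fitted separately or together is not stated, and no phase term is described.

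Sample Size: "Forty participants will be included in the study", with 30 to 36 expected to supply data after EMA acceptance. The Limitations section keeps patients who refuse EMA in the study for questionnaires and interviews. Table 1 places Brief-COPE, BDI-II and HADS at phases 1b, 2 and 3, and MINI, MADRS and HAM-A at phases 1a and 3 only.

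**The concern.** To say that coping helps more at phase 1 than later is to say that the coping effect depends on phase. Supporting it requires an estimate of the difference between effects, with an interval. A univariate logistic model has one predictor, so it has no room for a coping-by-phase term. Run within each time, it gives one odds ratio per phase. Run between times, it most naturally relates coping at one phase to case status at a later one, which is prospective prediction and not a comparison of effects. Neither use takes account of the phases coming from the same patients.

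With few cases per phase, the separate odds ratios will scatter by chance. The Clinical Implications section hopes to identify reliable signs at different times after stroke and to advise clinicians on them, so an apparent phase pattern that is only scatter could be carried forward as a finding.

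**Working it through.** **1. The plan's own figure.** 40 × 0.75 = 30 and 40 × 0.90 = 36, so the stated 30 to 36 reproduces. The article gives no significance level, effect size or power for the secondary aims, so there is no further figure to reproduce.

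**2. Patients and cases for the coping models.** EMA refusers still complete the questionnaires, so the Brief-COPE analyses could use up to 40 patients. The Background gives prevalences of 20-40% (depression) and 18-32% (anxiety). At an assumed 30%, cases per phase are 0.30 × 30 = 9, 0.30 × 36 = 10.8 and 0.30 × 40 = 12.

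**3. What the named model can estimate.** Item (2) at phase k fits logit P(case) = a_k + b_k × coping. The expectation concerns b_1 − b_2 and b_1 − b_3. These differences, and their standard errors allowing for repeated measures, are not outputs of the three fits.

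**4. If separate results were compared by significance.** Let each phase have the same true effect and power p.

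- Independent phases: P(phases disagree) = 1 − p³ − (1 − p)³, and P(phase 1 alone significant) = p(1 − p)².
- At p = 0.3: 1 − 0.027 − 0.343 = 0.63, and 0.3 × 0.49 = 0.147.
- At p = 0.5: 1 − 0.125 − 0.125 = 0.75, and 0.5 × 0.25 = 0.125.
- At p = 0.8: 1 − 0.512 − 0.008 = 0.48, and 0.8 × 0.04 = 0.032.

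Simulation of three logistic fits with equal true odds ratios of 0.3-0.5 per SD, 30% cases and n = 30-40 gave disagreement in about 45-71% of studies and phase 1 alone significant in about 3-14%. A repeat run (6,000 studies per setting, two-sided Wald 0.05, predictor correlation 0.6 across phases, latent outcome correlation 0 or 0.5) gave 42-73% and 3-15%. Its results with outcome correlation 0.5:

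| n | OR per SD | Power per phase | Phases disagree | Phase 1 alone |
|---|---|---|---|---|
| 30 | 0.5 | 29% | 55% | 13% |
| 30 | 0.3 | 63% | 63% | 8% |
| 36 | 0.5 | 36% | 62% | 12% |
| 36 | 0.3 | 75% | 51% | 5% |
| 40 | 0.5 | 40% | 63% | 12% |
| 40 | 0.3 | 81% | 42% | 3% |

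The odds ratios, significance level, case share within the document's range, and correlations are assumptions.

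**5. What a direct contrast could show.** Contrast of two log odds ratios, phase 1 against one later phase: z = (b_1 − b_2) / √(se_1² + se_2²), with independent phases and 30% cases. With effects expressed as reductions in odds per SD, simulated power at n = 30 / n = 36 is:

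- threefold at phase 1, none later: about 35% / 42%;
- twofold at phase 1, none later: about 18% / 23%;
- threefold at phase 1, 1.5-fold later: about 13% / 15%.

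The contrast addresses the stated expectation, but at this size it mainly gives a wide interval.

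**The case against.** The strongest reply has four parts.

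- **No decision rule is stated.** A reader might infer that a phase difference will be read from which phases reach significance. The article states neither such a rule nor a significance level, and odds ratios with intervals could be compared instead. This stands: the simulation shows what would happen under that practice, not what the plan prescribes. It does not remove the gap, because an informal comparison of separate intervals still gives no interval for the difference.
- **The methods are wider than within-time logistic fits.** A reader might infer that every model is fitted phase by phase. That is stated only for the logistic regressions, which also run between times. The physical-to-specific symptom expectation belongs to the autoregressive model, where the handling of phase is not stated. Coping also enters that model, but no phase term is described there either, so no named analysis estimates the expected change.
- **These are anticipated results.** They concern secondary aims of a 40-patient feasibility study, the dynamics are called exploratory, and a full protocol or analysis plan may hold more detail. This limits the weight. But the article does name a model for coping, and as named that model cannot address the stated expectation.
- **The harm is easily inflated.** Under equal effects, phase 1 is significant with at least one later phase not significant in about 23-38% of simulated studies. A reader might take this as the chance of concluding that coping protects only early. It includes studies where one later phase is also significant; phase 1 alone occurs in about 3-14%.

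**Conclusion.** The concern holds in a limited form. The article expects the effect of active coping to be larger at phase 1 than later, and the model it names for coping cannot estimate that difference or allow for repeated measures on the same patients. If separate results were compared by significance, which is likely but not stated, a constant effect would give discordant phases in roughly half to two-thirds of studies (about 45-71%), and the clear-cut early-only pattern in about 3-14%. These sizes rest on assumed odds ratios of 0.3-0.5 per SD, 30% cases, n = 30-40 and two-sided 0.05.

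For the autoregressive model the documents support only the observation that phase handling is unstated. They do not show that it is fitted wrongly. The point concerns a secondary aim and leaves the primary feasibility and validity analyses untouched. It is worth correcting because the better analysis uses data already planned.

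**What to change.** For the coping expectation, fit one repeated-measures model over phases 1b, 2 and 3, with Brief-COPE active coping, phase and their interaction.

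- **Outcome:** preferably the continuous HADS and BDI-II scores in a mixed model. If case status is wanted, use self-report cut-offs in a GEE with a small-sample variance correction. MINI, MADRS and HAM-A cannot serve in a three-phase model because they are taken only at phases 1a and 3.
- **Population:** all participants who complete the questionnaires, up to 40, including those who refuse EMA.
- **Claim:** report a phase difference only from the interaction estimate with its 95% CI. Otherwise, call the expectation descriptive.
- **Autoregressive model:** state how phase is handled, and base any claimed phase difference in lag paths on a direct contrast or label it descriptive.

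The cost is some extra analysis and no new data. The drawback is a wide interval, so the usual conclusion on phase differences will be that they are uncertain.

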### Research and Clinical Implications

#### Research Implications

Ecological Momentary Assessment using smartphone application is a wide area in terms of research perspectives. The great ecological validity of instantaneous capture of phenomenon in their real life contexts makes EMA method a promising perspective for research and knowledge in the field of psychopathology.

However, standard instruments still have to be developed. Recent published papers in different fields of psychology may be pieces of evidence that solid references are needed and that sharing protocols could help (Benarous et al., 2016; Mareva et al., 2016). We hopefully think that sharing and presenting the innovative protocol of the present work will contribute to develop EMA research. We expect this study to participate in the development of EMA research and methods in the area of psychological processes and more accurately in the study of populations with somatic and neurologic conditions.

The fact that we combined different assessment methods of psychopathology (i.e., self-report questionnaires, clinicians’ observation, EMA) is a main strength of this study. Indeed, the results will bring information regarding the validity of these different methods of psychological assessment.

Finally, the longitudinal EMA design of the study with three distinct phases at different times over a 4-month period is an original design for which feasibility has still to be informed.

#### Clinical Implications

Concerning the acute case of PSD and PSA etiopathogenesis, EMA research offers promising results so as to better understand the determinants, characteristics and the evolution of those emotional manifestations after a minor stroke. The EMA design of this study will help to clarify the biopsychosocial model of PSD and PSA (Aben and Verhey, 2006; Mast and Vedrody, 2006). Because of its particular ecological dimension, EMA makes possible to approach psychological phenomenon in real life environment. Thus, it enables to observe processes between behaviors, thoughts, emotions and environment. Our longitudinal EMA design could offers interesting results concerning those processes at different times after stroke.

We are expecting this study to contribute in the enhancement of diagnostic accuracy of psychiatric disorders and the detection of emotional distress in minor stroke population. We hopefully think the results of the present study could lead to identify specific reliable signs of depression and anxiety at different times after a stroke. Such results could help clinicians and care providers who work with stroke patients so as to facilitate the detection of emotional disorders by recommending them to focus on specific symptoms.

Finally, the remotely assessment of depression and anxiety using a smartphone application offers interesting perspectives for home-returned cares and follow-ups. Early supported discharge should be a better option for stroke patients (Mas and Inzitari, 2015) and is the main trajectory of minor stroke patients. The results of the present study will bring information concerning feasibility, validity and reliability of smartphone application psychological assessment after hospital discharge. Considering those results, further research could be suggested so as to develop a standard instrument for depression and anxiety screening after hospital discharge of stroke patients. Previous research in breast cancer population shown promising results in the field of mobile tool for screening depression (Kim et al., 2016). It still has to be developed in stroke population and it could lead to the improvement of the early supported discharge after a stroke by taking into account a remotely psychological follow-up.

### Limitations

The main limitation that could be mentioned is related to the respondent’s burden. It requires a substantial involvement for participants to answer EMA studies. Indeed, in our study there are three EMA phases during a period of 4 months, each one lasting 1 week. We are aware of this fact that is why we gave a major importance to make the study the less interfering and disturbing considering each participant schedule and daily life by using a quick smartphone electronic interview. Previous studies (Juengst et al., 2015; Maes et al., 2015) have shown that EMA participants well accept and are satisfied with this method.

Previous studies showing EMA in stroke population used five daily evaluations against only four in the present study (Lassalle-Lagadec et al., 2012; Sibon et al., 2012; Jean et al., 2013; Mazure et al., 2014). This main methodological difference is explained by the fact that previous research had no repeated EMA design. This reduction in the number of daily assessments has been chosen given the longitudinal perspective of the repeated EMA phases. Indeed, by reducing this number we expect to prevent a reduction in the participation at follow-up phases and so optimizing the quantity of data collected.

As it was previously underlined in studies focusing on methodological issues of EMA (Telford et al., 2012), answering to multiple daily psychological assessments should involve some reflection about biases and ethical concern. This issue is a general research issue known as the Hawthorne effect or the Participation to Research Effect (McCambridge et al., 2014a,b), but it could have a greater resonance considering EMA studies. Indeed, the repetitive confrontation to questions about negative daily life experiences could be considered as a double-edged sword: it forces people to remind and confront to bad experiences on one hand, but it can also make them more aware of their own experiences and needs so that they can eventually adjust to it (Shiffman, 2009; Telford et al., 2012; Runyan and Steinke, 2015).

We will give special concern to participants in the study and ethical requirements allow to help and to offer treatments for people who eventually will report mental distress and suffering during each phase.

Even the potential therapeutic effect of paying attention to self-feelings several times a day during EMA weeks could be a positive consequence for respondents, it could also be a significant bias of the study. However, the design of our study offers a possibility to test this bias. Indeed, we will include participants in the general study even if they refuse to participate to the smartphone application protocol. Those participants will not answer to EMA but they undergo the same exact procedure concerning questionnaires and interviews. We will then compare the evolution of psychological outcomes assessed by self-report questionnaires and clinician’s observation of the participants to the smartphone protocol to the individuals who refused to participate in this part of the study.

The compliance of participants is another important point that could impact the results because of the repeated daily assessment design of the study. This bias is a fatigue effect that have previously been studied in EMA studies in stroke population (Johnson et al., 2009b) and did not seemed to have a significant impact on participation as a function of study duration. Nevertheless, this study had no repeated design considering EMA. Thus, we will pay close attention to this potential effect in our analysis of feasibility. We described in the method section the particular implication of the investigator at each EMA phase so as to reinforce motivation of respondent and also the reduction of the number of daily prompts compared to previous studies so as to prevent the importance of potential fatigue effect because of the study design.

The point of the generalization of results also should be considered. The purpose of the study is to focus on mild stroke population given their particular health care compared to more severe stroke situations generally implying more medical concern and professional involvement. Nevertheless, the understanding of the pathogenesis of post-stroke mental disorders is important in both mild and severe stroke and ecological methods such as described in this article have been highlighted as promising perspective. It is clear that the present methods do not suit situations of more severe stroke with motor or cognitive impairments and that is why patient with motor or cognitive impairments are not included. Thus, the interpretation of results will hardly be generalizable to general stroke population. To date, the incompatibility with disability situations is one of the main limitations of EMA development in research. Current EMA instruments seem not to suit disability situations and so further research should design and evaluate suitable EMA methods for more severe. For example, daily repeated vocal recordings to automatically question could be used with motor dysfunction of upper limbs or visual difficulty after stroke instead of smartphone application with questions to read on different screens to scroll. Such designs would imply different experimental conditions and probably other biases that future study would have to take on.

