##### At hospital discharge (phase 1b)

The psychologist investigator calls the patients to have an appointment in the first days following hospital discharge. Patients are met at home in order to start the EMA procedure. During this appointment, patients fill self-report questionnaires assessing depression, anxiety, quality of life and coping strategies with stroke related stress. After that, the investigator either installs the study application on patients’ personal devices or lent a device during the EMA procedure for patients who do not possess a smartphone. The content of the application is displayed and patients are trained to use it in order to resolve technical concerns and questions. After 2 days, patients are called by the investigator in order to check any problem and to reinforce the motivation to keep answering the prompts. At the end of the week, patients are informed by a phone call that they can disconnect from the app.

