#### Data Analysis

##### Outcomes and statistical methods for primary objectives

Feasibility and acceptability of the EMA method will be assessed by examination of acceptance and compliance rate, fatigue effects and reactivity to assessment: completion rate during each week, participation at follow-up weeks (phases 2 and 3), missing data and assessment duration across time during each phase. Descriptive analysis will be performed to describe feasibility and acceptability. Compliance will be assessed as the completion rate of EMA questionnaires. This rate will be calculated as the ratio of completed questionnaires to all sent questionnaires within each phase (four questionnaires per day during 7 days for each participant). Follow-up participation will be the ratio of number of participants at phase 2 and 3 to the number of participants at inclusion (phase 1). Fatigue effect will be calculated as the evolution of the within-day mean of missing data. Reactivity to EMA assessment will be estimated by comparing anxiety, depression and quality of life scores (self-reported questionnaires and clinicians’ ratings) of EMA participants to other participants (not involved in the EMA part of the study, more information is given in the limitations section below).

Validity of the method will be examined by using three different EMA indexes consisting in different aggregation of anxious and depressive symptoms assessed with EMA for each participant: a global anxiety and depression index (including all 11 symptoms assessed), a specific depression index (including sadness, anhedonia, fatigue, concentration difficulties, negative thoughts, pessimism) and a specific anxiety index (including anxiety, agitation, physical tension, irritability, concentration difficulties).

Validity will be assessed by using Pearson correlations between EMA indexes with self-reported questionnaires’ scores and clinicians’ ratings. Only participants with a satisfying minimum within- and between-day compliance will be included in this analysis (i.e., at least 5 EMA questionnaires filled). We will observe associations between: the global EMA index and the overall score of the HADS; the depression EMA index with the BDI score, the HADS depression subscale score and the MADRS score; the anxiety EMA index with the HADS anxiety subscale score and the HAM-A.

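### The planned test of EMA reactivity is a comparison with about 4 to 10 self-selected refusers, so it can only be descriptive; it should be specified as one baseline-adjusted contrast and not presented as a test of the bias

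*Protocol article*

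**What the plan says.** - **Size and acceptance (Sample Size).** "Forty participants will be included in the study", "an acceptance rate between 75 and 90% is expected", and so "we expect data from 30 to 36 participants to perform analysis".
- **Comparator (Limitations).** The authors recognise that repeated self-assessment may itself change mood, and reply that "the design of our study offers a possibility to test this bias". The means is that "we will include participants in the general study even if they refuse to participate to the smartphone application protocol". Refusers undergo the same questionnaires and interviews, and the change over time in EMA users is then compared "to the individuals who refused to participate in this part of the study".
- **Analysis (Outcomes and statistical methods for primary objectives).** "Reactivity to EMA assessment will be estimated by comparing anxiety, depression and quality of life scores" between EMA users and the other participants, on self-report and clinician ratings. The sentence refers the reader to the Limitations section for more detail.
- **Timing.** The clinician ratings at phase 1a are made in hospital. At phase 1b the questionnaires come first: "After that, the investigator either installs the study application". By Table 1, self-report scales are repeated at phases 2 and 3, and clinician ratings at phase 3.
- **Contact.** EMA users are telephoned after two days in each EMA week, and again at the end of the week at phase 1b.

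**The concern.** Reactivity is one of the outcomes under the primary objective, and the Limitations section relies on this comparison to deal with a bias that it calls potentially significant. Three features limit what the comparison can show.

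1. **Self-selection.** People who decline to report mood on a phone several times a day may differ in mood, fatigue or ease with the device. The Limitations section does not mention this.
2. **Size.** The comparator is whatever remains of 40 after 75 to 90% have accepted. The article gives neither that number nor what it implies.
3. **Loose specification.** The analysis section speaks of scores and the Limitations section of change over time. A comparison of scores at phase 1a or 1b would measure selection or chance only, because no EMA has yet taken place.

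The extra telephone calls are a further difference between the groups that is not EMA itself.

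If the result were reported as a test, a difference could not be attributed to EMA, and the lack of one would say little about whether reactivity exists.

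**Working it through.** **The plan's own figure.** 40 × 0.75 = 30 and 40 × 0.90 = 36, which reproduces the stated 30 to 36.

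**Refusers.** Since refusers stay in the study, they number 40 − 30 = 10 down to 40 − 36 = 4. These are expectations before any follow-up loss.

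**Assumptions.** The article gives no alpha, SD or effect size for this comparison. I assume two-sided 5%, scores in SD units and a two-sample t-test with 38 degrees of freedom (critical value 2.024).

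**Unadjusted precision.** SE = √(1/n₁ + 1/n₂); half-width = 2.024 × SE; power from the non-central t.

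| | 30 v 10 | 36 v 4 |
|---|---|---|
| SE (SD) | 0.365 | 0.527 |
| 95% CI half-width (SD) | 0.74 | 1.07 |
| Power for 0.5 SD | 27% | 15% |
| Power for 0.8 SD | 57% | 32% |
| Difference detectable with 80% power (SD) | 1.05 | 1.52 |

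**With baseline adjustment.** The residual SD shrinks by √(1 − ρ²). The baseline correlation ρ is not in the article; I take 0.5 to 0.7, which gives factors of 0.866 and 0.714.

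| | 30 v 10 | 36 v 4 |
|---|---|---|
| Half-width, ρ = 0.5 (SD) | 0.74 × 0.866 = 0.64 | 1.07 × 0.866 = 0.93 |
| Half-width, ρ = 0.7 (SD) | 0.74 × 0.714 = 0.53 | 1.07 × 0.714 = 0.76 |
| Power for 0.5 SD, ρ = 0.5 | 34% | 19% |
| Power for 0.5 SD, ρ = 0.7 | 46% | 25% |

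The adjusted half-width is therefore still roughly 0.5 to 0.9 SD.

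**Size needed, for scale.** With k EMA users per refuser and 80% power for 0.5 SD, refusers = (1 + 1/k)(1.960 + 0.842)²/0.5². This gives 42 refusers and 126 EMA users at k = 3, or 35 and 315 at k = 9. Self-selection would remain at any size.

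**What each time point can carry.**

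| Time point | EMA already undergone | Use |
|---|---|---|
| Phase 1a ratings | none | baseline |
| Phase 1b questionnaires | none | baseline |
| Phase 2 questionnaires | at least the first week | reactivity contrast |
| Phase 3 ratings and questionnaires | two weeks (the third comes after the interview) | reactivity contrast |

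**The case against.** The strongest reply is that the article already plans the sensible contrast. The analysis section points to the Limitations section, which compares change over time. On that reading, measurements taken before EMA are a strength: they give a clean baseline, and phases 2 and 3 both follow at least one EMA week. This stands. A reader might infer that the two sections contradict each other outright, or that the order of events at phase 1b spoils the comparison. The documents support neither reading. The analysis section is loosely worded, and the timing rules out only a comparison of scores at phases 1a or 1b.

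A reader might also infer that the authors will take a null result as proof of no reactivity. The article does not say so. It describes feasibility and acceptability descriptively, sets no test or decision rule for reactivity, and lists no expected result for it. The wording about testing the bias is itself hedged.

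Finally, a small refuser group is inherent in a 40-person feasibility study, and keeping refusers at all is to the authors' credit. Compliance and validity do not depend on this contrast, and the abstract defines feasibility by participation and compliance. That limits the seriousness of the point but does not remove it. The number of refusers follows from the stated figures, and the Limitations section discloses neither that number nor the self-selection.

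**Conclusion.** The point holds in a limited form. The comparison with refusers is confounded with acceptance of EMA and with extra telephone contact, and it rests on about 10 down to 4 people. Its 95% CI half-width is about 0.74 to 1.07 SD unadjusted, and roughly 0.5 to 0.9 SD after baseline adjustment. It can describe, but it cannot test the bias in any useful sense, and a null result would leave moderate to large reactivity open. Adjustment removes only the selection captured by the baseline scores.

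The size rests on the expected acceptance rate, on the 40 including refusers (as Sample Size and Limitations together indicate), and on the assumed two-sided 5% and baseline correlation of 0.5 to 0.7. Follow-up loss would widen the intervals. The change should be made, but the other primary-objective outcomes do not depend on it.

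**What to change.** 1. **Specify one contrast.** Bring the analysis section into line with the Limitations section: compare later scores between EMA users and refusers, adjusted for the pre-EMA value. Use phase 1b BDI-II, HADS and WHOQOL-BREF as baseline for phases 2 and 3, and phase 1a MADRS and HAM-A for phase 3. Report each as a difference with its 95% CI. State that phase 1a and 1b scores serve only as baseline.
2. **Reword the claim in Limitations.** Replace the statement about testing the bias with one along these lines: this is a descriptive, non-randomised comparison with about 4 to 10 self-selected refusers; EMA users also receive extra calls; a null result cannot exclude moderate to large reactivity.
3. **Optional and supportive only.** The trend of the EMA indexes within each week among EMA users may be added. It has no unexposed comparator and must be described as mixed with natural recovery.

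All the data for this are already scheduled in Table 1, so no visit or measurement is added. The cost is a weaker claim about reactivity.
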